### Recruitment

Recruitment is based on the LIVES longitudinal study and internet-self-help forums. All participants who reported difficulties with adjustment after marital bereavement or separation or divorce in the LIVES study receive an information letter about the self-help programme, with a link to the study website, from the LIVES study coordinator. Additionally, information about the intervention with a link to the study website is posted on several internet-based self-help forums.

### Eligibility criteria

All interested adults are required to complete baseline screening questionnaires and a telephone interview for assessing eligibility prior to randomization.

Inclusion criteria are:Experience of marital bereavement or a separation or divorce more than 6 months prior to enrolment in the studySeeking help for coping with prolonged grief symptoms, psychological distress or the psychosocial adaptation to a life without the partnerHaving access to an internet connectionMastery of the German languageProvision of informed consent

Exclusion criteria are:Severe psychological or somatic disorders which need immediate treatment and acute suicidality (Beck Depression Inventory suicide item > 1 or suicidal ideation in the telephone interview).No emergency plan: in the telephone interview, an emergency plan will be developed that specifies a health care professional, to whom participants can turn in an acute crisis. If no such person or health care service can be found, individuals are excluded from the intervention.Concomitant psychotherapy, or prescribed drugs to treat depression or anxiety, if the prescription or dosage has changed in the month prior or during the self-help intervention.Inability to follow the procedures of the study, e.g. due to comprehension problems.

### Description of the intervention

The intervention is a guided 10-week internet-based self-help programme. The 10 text-based sessions are described in detail in Table 1. Participants are encouraged to work through one session a week and to complete the assignments. One session takes between 45 min and 60 min. The first two sessions include general information about interpersonal loss and an assessment of the current personal situation. Sessions 3 to 5 focus on resources and restoration-oriented interventions for fostering positive thoughts and emotions as well as self-care. Sessions 6 and 7 consist of loss-oriented interventions for accepting memories and pain and address unfinished business. Sessions 8 and 9 again include restoration-oriented interventions, focusing on creating a new life without the partner and social relationships. The last session addresses the redefinition of the relationship to the lost person. The sessions for bereaved and separated or divorced participants are identical apart from adaptations in the first session (psychoeducation) and the sixth session (accepting memories and telling the story of the loss).

**Table 1 Tab1:** Outline of the 10 self-help sessions of the internet-based intervention

1. Psychoeducation	Information about the self-help intervention, grief reactions, reactions to separation, predictors and treatment of complicated grief
2. Assessment of current situation	Information about and assessment of emotions in the context of the interpersonal loss, changes in life since the loss and obstacles for a positive adaptation
3. Fostering positive thoughts and emotions	Information about emotion regulation and cognitive-behavioural strategies to promote positive thoughts and emotions Protocols for practising these strategies in daily life
4. Finding comfort	Suggestions for self-soothing strategies and exercises to promote positive feelings (e.g. diary for positive experiences)
5. Self-care	Checklists for current physical, emotional and practical self-care, formulation of self-care goals and suggestions for implementing self-care behaviour in daily life
6. Accepting memories and pain	Writing tasks to integrate painful memories of the loss into the autobiographical memory and to be able to tell the story of the loss
7. Unfinished business	Identification of unfinished business and regrets, writing tasks to formulate unfinished business and to find ways to put issues at rest
8. Creating a new life without the partner	Identifying changes in daily life since the loss and sources of support and strengths before and after the loss Information about post-traumatic growth Identifying and activating resources in daily life
9. Social relationships	Clarifying current relationships using a sociogram Defining goals related to social relationships, e.g. changing relationships, building up new social contacts, and suggestions for promoting social well-being
10. Redefinition of the relationship to the lost partner	Writing a farewell letter to the lost partner: saying good-bye and telling the lost partner about the future importance of the loss and how the participant will continue life without the lost partner

During the work with the text-based sessions, participants receive email support by psychologists of the Department of Clinical Psychology and Psychotherapy of the University of Bern. These weekly emails acknowledge and motivate participants in their work with the self-help programme and provide a weekly structure and support for technical problems. Participants can contact their supporters anytime with questions via a contact button in the self-help programme. The email-supporters are supervised by a fully trained psychotherapist.

### Measures

Figure 2 (the SPIRIT figure schedule of enrolment, interventions, and assessments) gives an overview of the measures with the timing of the assessment. All self-report questionnaires are completed online. Baseline measurement is at *t*
_0_, post-measurement *t*
_1_ is 12 weeks after the start of the programme or waiting condition, post-measurement *t*
_2_ is after 24 weeks, and the follow-up measure *t*
_3_ will be completed only by the waiting control group 24 weeks after their start of the intervention, i.e. 36 weeks after baseline.

**Fig. 2 Fig2:**
[figure not shown]
SPIRIT figure: schedule of enrolment, interventions, and assessments

#### Primary outcome measures

Grief symptoms are assessed using the German version of the Texas Revised Inventory of Grief [23]. The Texas Revised Inventory of Grief is a widely used measure to assess the severity of grief symptoms. A recent factor analysis identified three factors for emotional response, thoughts, and non-acceptance regarding a loss [24]. The German version of the Texas Revised Inventory of Grief is a 16-item measure to assess the severity of grief symptoms, from 1 = completely true to 5 = completely false.

Psychopathological distress is assessed using the German version of the Brief Symptom Inventory, a widely used 53-item measure to assess a broad range of somatic and psychopathological symptoms within 7 days prior to completing the questionnaire [25]. Factors include depressed mood, somatic symptoms, information processing deficits, and interpersonal insecurity [26]. Answer categories range from 0 = not at all to 4 = very much.

Depressive symptoms are assessed with the German version of the Beck Depression Inventory II [27]. This measure consists of 21 items on a scale from 0 to 3.

#### Secondary outcome measures

Loneliness is assessed using the De Jong Gierveld Short Scale for Emotional and Social Loneliness [28]. This is a six-item scale with answer categories from 0 = no to 5 = yes.Embitterment is assessed with the short version of the Embitterment Scale, which consists of six items rated on a scale from 0 = I do not agree to 4 = I agree [29].Life satisfaction is assessed with the German version of the Satisfaction with Life Scale [30, 31]. It consists of five items with answer categories from 1 = completely disagree to 7 = completely agree.Session-related outcomes. We included nine items related to specific sessions of the intervention, e.g. self-rated knowledge about grief symptoms, self-care, self-soothing strategies, satisfaction with social relationships or the current life situation. Items are rated on scale from 1 = very little to 10 = very much.Satisfaction with the self-help programme. Six items assess the evaluation of the quality of and the satisfaction with the intervention, and six items assess effects of the intervention related to mechanisms of change, i.e. mastery experiences, clarification experiences or insight, problem actuation, and resource activation. Response categories range from 1 = not at all to 4 = very much.

#### Predictors and moderators

Computer literacy is assessed using the first seven items of the Computer Literacy Scale for Older Adults [32]. They assess experiences with the computer and the frequency with which participants engage in different computer-related tasks.Demographic variables include sex, age, education, overall self-rated health, and details about the marital history and the loss of the partner or the separation or divorce.Criteria for a persistent complex bereavement disorder according to the Diagnostic and Statistical Manual of Mental Disorders [7] are assessed in the telephone interview.Suicidality is assessed in the telephone interview using the suicidality questions of the Brief Psychiatric Rating Scale [33].Adherence and completion data, as well as data on the duration and the intensity of the use of the self-help intervention are collected within the platform.

### Data collection and management

Data are assessed using online-questionnaires programmed in Qualtrics [34]. Data integrity is enforced through a variety of mechanisms, i.e. referential data rules, valid values, range checks, and consistency checks. The option to choose a value from a list of valid codes and a description of what each code means is available where applicable. Checks are applied at the time of data entry into a specific field. In addition, data on the use of the self-help sessions are collected within the platform. All data will be saved in an anonymous way only identified by a code that is not related to the participant’s identity. Servers are protected by high-end firewall systems. Only the researchers directly involved in the study have access to the data.

### Statistical analysis

Analysis will be conducted according to the intention-to-treat paradigm. Firstly, we will analyze the extent of missing data, explore the missing data patterns and determine the type of missing data (missing completely at randomization, missing at randomization, not missing at randomization). If the missing mechanism is missing at randomization, we will use multilevel regression analyses, which allow a different number of measurement points per participants and are thus less sensitive to missing data. We will include time (pre versus post-intervention measures and post-intervention versus follow-up measures), group (immediate access versus control condition), event (bereavement versus separation or divorce) and interaction terms as predictors of the outcome variables. Cohens *d* will be calculated as effect size for all observed outcome variables. To analyze the longitudinal interplay of predictor variables, we will conduct structural equation models. Analysis will be conducted in SPSS and Mplus.

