**Methods:**

The design is a randomized controlled trial with a waiting control condition of 12 weeks and a 24-weeks follow-up. At least 72 widowed or separated participants will be recruited via our study website and internet forums. Primary outcomes are reductions in grief symptoms, depression and psychological distress. Secondary outcome measures are related to loneliness, satisfaction with life, embitterment and the sessions.

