### Sample size

We specified the sample size needed for the different analyses conducting a power analysis based on a probability level of 0.05 and a power of 0.80 with G*Power [21] and a power analysis calculator for structural equation models [22]. To test the efficacy of the intervention compared with the control condition, we expected a large effect of *d* = 0.80. Power analyses indicated a necessary sample size of 42 individuals for this most basic analysis. For the analysis of several predictor variables, as well as moderation and mediation effects using structural equation modelling, we assumed moderate effects of *r* = 0.30. Power analyses resulted in a sample size of 138 participants. Anticipating a drop-out rate of 40% at the 6 month follow-up, we aim at recruiting between 72 and 220 participants at baseline.

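### The efficacy model gives each arm its own baseline mean; this is valid, but less precise than a common baseline or adjustment for the t0 score

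*Protocol article*

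**What the plan says.** The Statistical analysis section sets out the model for the outcome variables. If data are missing at random, "we will use multilevel regression analyses, which allow a different number of measurement points per participants". The predictors are then listed: "We will include time (pre versus post-intervention measures and post-intervention versus follow-up measures), group (immediate access versus control condition", followed by type of loss (event) and interaction terms. The list contains no baseline-score covariate and no constraint on the arms' baseline means. Baseline severity appears in the Objectives only as a moderator.

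The Sample size section uses "a probability level of 0.05 and a power of 0.80" and, for efficacy, "we expected a large effect of *d* = 0.80". It concludes: "Power analyses indicated a necessary sample size of 42 individuals for this most basic analysis". On recruitment it says: "Anticipating a drop-out rate of 40% at the 6 month follow-up, we aim at recruiting between 72 and 220 participants at baseline". The abstract commits only to the lower end: "At least 72 widowed or separated participants will be recruited via our study website and internet forums". Under Study design, the waiting group receives the programme 12 weeks after baseline, so t1 is the only time point at which the randomised arms can be compared as treated against untreated.

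**The concern.** Because time includes the pre level and group is a predictor in its own right, the model estimates two baseline means, one per arm. Randomisation implies a single expected baseline, so any observed difference at t0 is chance. The interaction subtracts that chance difference in full, whereas only a fraction rho of it is expected to carry over to t1. The rest enters the treatment estimate as noise.

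Two things are at stake for grief, distress and depression alike. One is power at the lower end of the recruitment range. The other is sensitivity to chance imbalance: given an observed t0 difference D between the arms, the change-score contrast is shifted by (1 - rho) x D through regression to the mean. The t0 scores are already collected, so the information needed to avoid this is at hand.

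**Working it through.** **Inputs.** From the Sample size section: alpha 0.05, power 0.80, d = 0.80, 42 for the efficacy comparison, 40% dropout at 6 months, 72 to 220 recruited. Assumed, because the article does not state them: 1:1 allocation, equal variances at t0 and t1, d in units of the raw-score SD, and rho from 0.4 to 0.7.

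**Step 1: the plan's own figure.** A two-sample t-test with d = 0.80 (noncentral t) has power 0.817 one-sided and 0.716 two-sided with 21 per arm. The smallest total giving 80% power is 42 one-sided and 52 two-sided. The stated 42 is therefore reproduced, but only as a one-sided test that uses no baseline information. Allowing for dropout, 42 / (1 - 0.40) = 70, close to the stated 72; in reverse, 72 x 0.60 = 43.2, about 43 completers.

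**Step 2: variance with complete data.** Relative to a comparison of post scores alone:

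- planned interaction (difference in change): 2(1 - rho)
- baseline-adjusted or common t0 mean: 1 - rho²
- ratio of planned to adjusted: 2 / (1 + rho)

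The ratio exceeds 1 for every rho below 1.

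**Step 3: variance under the planned multilevel fit.** A likelihood fit also uses the t0 scores of people who lack t1. With 72 randomised and 43 completing (60%), missing at random, the free-baseline variance becomes (1 - rho²) + 0.6(1 - rho)². The ratio to the common-baseline model is 1 + 0.6(1 - rho)/(1 + rho). At rho = 0.5 this is 1 + 0.6 x 0.5/1.5 = 1.20.

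| rho | Excess variance, complete data | Excess variance, 72 randomised and 43 completing |
|---|---|---|
| 0.4 | 43% | 26% |
| 0.5 | 33% | 20% |
| 0.6 | 25% | 15% |
| 0.7 | 18% | 11% |

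**Step 4: power at d = 0.80, planned versus adjusted.** One degree of freedom is charged to the adjusted model.

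| rho | 21 per arm, complete, two-sided | 21 per arm, complete, one-sided | 72 randomised and 43 completing, two-sided |
|---|---|---|---|
| 0.4 | 63.7% vs 78.8% | 75.2% vs 87.2% | 70.3% vs 79.7% |
| 0.5 | 71.6% vs 83.1% | 81.7% vs 90.2% | 77.0% vs 84.0% |
| 0.6 | 80.7% vs 88.5% | 88.6% vs 93.8% | 84.7% vs 89.2% |
| 0.7 | 90.4% vs 94.3% | 95.0% vs 97.3% | 92.6% vs 94.8% |

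**Step 5: chance imbalance.** With 21 per arm the standard error of the t0 difference is √(2/21) = 0.31 SD. An imbalance of that size shifts the change-score contrast by (1 - 0.5) x 0.31 = 0.15 SD at rho = 0.5.

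**The case against.** The strongest reply is that nothing here is an error. A group-by-time multilevel model is standard, unbiased under randomisation and keeps its type I error. The article is also condensed: a full analysis plan could impose a common baseline within the same framework. The first part stands and limits the point to efficiency. The second stands only in part, because the article does list the model's terms, and those terms as written give free baselines.

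The size is also open to challenge, and most of that challenge stands:

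- The complete-data figures overstate the loss for a model chosen because it tolerates unequal numbers of measurements.
- The 40% dropout is stated for 6 months, so more than 43 may contribute at 12 weeks. With an assumed 20% loss from 72 (about 29 per arm, complete data, two-sided), the planned model has 85%, 92% and 97% power at rho 0.5, 0.6 and 0.7.
- Recruitment may reach 220, since "Power analyses resulted in a sample size of 138 participants" for the secondary models.
- Much of the two-sided shortfall comes from sidedness: a plain post-score comparison at 42 also has only 71.6%. One-sided, the planned interaction meets 80% from rho = 0.5 upwards.
- Adjustment is not strictly free. It spends one degree of freedom, and estimating the slope costs about one further point of power at this size, which the table leaves out.

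A reader might infer that the planned test is weaker than the simple comparison behind the 42. With complete data that requires rho below 0.5. With the dropouts' baselines used, it requires 1.6 - 1.2rho - 0.4rho² to exceed 1, which means rho below about 0.44. The article gives no correlation, and does not say whether d = 0.80 refers to post scores or to change, so this inference is not supported.

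**Conclusion.** The point holds as a matter of precision. As listed, the model estimates the 12-week effect with an avoidable excess variance of roughly 11% to 26% under the multilevel fit at the recruitment floor, and 18% to 43% with complete data, for rho between 0.7 and 0.4. In two-sided power at the floor, the difference is about 9 points at rho 0.4 and 2 points at rho 0.7 under the multilevel fit, and about 15 and 4 points with complete data. The direction is certain for any rho below 1, apart from the small cost of the slope in the covariate form. The size is not certain, because rho, the 12-week dropout and the sidedness of the test are not stated.

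It would go too far to call the planned analysis biased or invalid, or to say that this choice alone leaves the trial underpowered. The documents support neither: the interaction is a valid estimate, and the figures above are for the smallest sample that the article allows.

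**What to change.** Keep the multilevel framework and add one sentence to the Statistical analysis section. For each primary outcome, the primary efficacy estimate is the t1 group difference from a longitudinal model in which the arms share a common t0 mean, with event retained as already planned. An essentially equivalent option is the t1 difference adjusted for that outcome's own t0 score. The common-mean form has the advantage that participants who lack t1 stay in the model.

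The change needs no new data, visits or participants. The only statistical cost is one degree of freedom, with a slope to estimate, if the covariate form is used.

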## Discussion

The results of this study will provide insight into the acceptance and efficacy of an internet-based self-help intervention for adults who experience grief symptoms, psychological distress or adjustment problems in daily life after marital bereavement or separation or divorce. The outcomes for bereaved and separated or divorced participants will be compared. The analysis of other moderator variables may further aid future selective indication and adaptations for different needs.

Limitations of this study include the self-selectivity of the sample. It may be possible that older adults who are willing to take part in an internet-based self-help intervention have more cognitive resources and a higher education level.
